## Methods/design

This study is a prospective randomized controlled trial with a two-armed parallel design and 1:1 allocation ratio. Flow through the study is presented in Fig. 1. This study has been approved by the Health Research Ethics Board of Alberta Cancer Committee (HREBA.CC-16-10-10). The approved study will be reviewed annually by the HREBA.CC until completion. Any amendment to the protocol which may impact on the conduct of the study will require formal modification and approval by the HREBA.CC prior to implementation, and will be described transparently in subsequent reports. The study will be performed according to the Declaration of Helsinki. The study was registered at ClinicalTrials.gov before recruitment of the first participant (NCT03049384, first posted in February, 2017). The research will be conducted at a single site (Faculty of Kinesiology, University of Calgary, Alberta, Canada). This study protocol is written in accordance with the SPIRIT guidelines [63] (SPIRIT Checklist provided in Additional file 1).

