### Sample size

An a priori sample size estimation was performed using G*Power 3 (v3.1.2–3.1.9 [66]). The hypothesis was treated as a time × treatment (within-between) interaction for the primary outcome measure of score on the FACIT-F. A standardized mean difference of 0.44 was used, as reported in a 2012 Cochrane review for comparisons of CRF following an exercise intervention or control, from a total of 539 cancer survivors after anti-cancer therapy [29]. Using an α level of 0.05, a 1 - β of 0.8, the total sample size was calculated as 44. Potential loss to attrition was estimated as 15%, based on previous reports from supervised exercise interventions in cancer survivors post-treatment (e.g. [67]), and thus the total sample size was calculated as 52.

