### Follow-up

Six and 12 months after the exercise interventions, participants will be contacted via phone or email to complete the FACT-F scale, ESAS-r tiredness scale and the GLTEQ.

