### Intended statistical analysis

Data will be analysed after data collection is complete, and no interim statistical analysis will be performed. Descriptive statistics will be used for demographic and clinical variables measured at baseline for each group. Frequencies and percentages will be used for categorical variables and the mean ± standard deviation (or median and range) will be used for continuous variables. To account for any differences in loss to follow up between groups, the primary analysis will be conducted on an intention-to-treat basis. For the primary outcome of FACIT-F score between treatment arms over time, data will be analysed with linear mixed models using R [123] and lme4 [124]. “Treatment arm” will be included as a fixed effect and “participant” as a random effect. Parameters will be estimated using restricted maximal likelihood. The Kenward-Roger approximation for degrees of freedom will be used when evaluating the significance of effects. This produces optimal type I error rates (neither anti-conservative nor overly sensitive to sample size) [125]. Secondary analyses will be performed to assess adjustments for protocol deviations (per protocol analysis). Statistical code will be made openly available upon publication of the results. A minimum of a 3-point difference in FACIT-F score will be considered clinically relevant [126]. For secondary outcomes that are assessed pre- and post-intervention only (e.g. neuromuscular measures, sleep parameters, blood biomarkers), two-way mixed design ANOVA will be used (group [tailored vs. traditional] × time [pre- vs. post-intervention]). In this case, missing data will be dealt with using list-wise deletion. Following a significant interaction, pairwise comparisons will be conducted with a Bonferroni adjustment. The threshold for rejecting the null hypothesis will be *p* < 0.05. For main and interaction effects, partial eta squared will be computed as an effect size estimate. Effect sizes for pairwise comparisons will be reported as Cohen’s *d* [127, 128]. This will be supplemented with 95% confidence intervals for mean differences. Further exploratory analysis will be labelled as such in later reporting.

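### The type I error assurance covers only the Kenward-Roger degrees of freedom; with a random participant intercept it does not extend to a multi-visit arm × time test of FACIT-F

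*Protocol article*

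**What the plan says.** Under Sample size, the Protocol article frames the primary hypothesis as an interaction: "The hypothesis was treated as a time × treatment (within-between) interaction for the primary outcome measure of score on the FACIT-F". Under Intended statistical analysis, FACIT-F over time is analysed by a linear mixed model in R with lme4 and restricted maximum likelihood. Treatment arm is the only fixed effect named, and the only random term is "participant” as a random effect". Significance is judged with Kenward-Roger degrees of freedom, and the next sentence reads: "This produces optimal type I error rates (neither anti-conservative nor overly sensitive to sample size".

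Table 2 schedules FACIT-F, from baseline on, at Lab Visit #2, weeks 3, 6 and 9, Lab Visit #4, and months 6 and 12. The Follow-up section confirms the late assessments: "Six and 12 months after the exercise interventions, participants will be contacted via phone or email". Two-way ANOVA is reserved for secondary outcomes measured only before and after the intervention, which implies that the primary model uses more than two visits. The article does not say which visits enter that model.

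**The concern.** Kenward-Roger adjusts degrees of freedom and small-sample standard errors for the covariance model that has been fitted. It does not correct a covariance model that is wrong.

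If participant enters as an intercept, the lme4 model has one between-person variance and independent residuals of equal variance. Any two scores from one person then have the same correlation, whatever the interval between them, and everyone changes at the same underlying rate within an arm. Both assumptions are strong for a self-reported score followed for over a year in a deliberately heterogeneous cohort with individually varied exercise.

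Every arm × time contrast is then tested against one pooled within-person residual. If that residual does not match the variance of the change from baseline to Lab Visit #4, the primary p-value and confidence interval are miscalibrated. With 44 to 52 participants, one primary test at 0.05 and an unblinded self-report outcome, either direction matters: false positives if too liberal, lost power if too conservative.

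**Working it through.** **The plan's own figure.** "A standardized mean difference of 0.44 was used" gives f = 0.44/2 = 0.22. The G*Power within-between formula is λ = N·m·f²/(1−ρ), where m is the number of measurements. Taking m = 2 and ρ = 0.5 (both assumed; the article states neither), N = 44 gives λ = 44 × 2 × 0.0484/0.5 = 8.52 on 1 and 42 df, and power 0.814. N = 42 gives 0.795. So 44 reproduces, and 44/0.85 = 51.8 gives 52. With m = 7 the same formula would ask for 22. The sample size therefore matches a two-visit interaction test.

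**What the random-intercept test does.** Take complete data with 22 per arm ("two-armed parallel design and 1:1 allocation ratio", N = 44). The arm × time contrasts use the pooled within-person residual on (N−2)(m−1) df, taken here as what Kenward-Roger gives in balanced data. The expected residual is v̄ − c̄, the mean variance minus the mean covariance over pairs of visits. For the baseline-to-Lab Visit #4 change, the ratio of true to assumed variance is

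R = (v₀ + v₄ − 2c₀₄) / [2(v̄ − c̄)].

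Treating the residual as known, the approximate true error is P(|Z| > t_crit/√R). With two visits, v̄ − c̄ is exactly half the change variance, so R = 1 and nothing goes wrong. Under equal correlation R = 1 as well.

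**Five visits (weeks 0, 3, 6, 9, 12), 168 df, t_crit = 1.974.** All correlations are assumptions.

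- Pure autoregression, 0.8 per 3-week step: correlation of week 0 with week 12 = 0.8⁴ = 0.410. Mean correlation = (4×0.8 + 3×0.64 + 2×0.512 + 0.410)/10 = 0.655. R = 0.590/0.345 = 1.71; 1.974/√1.71 = 1.51; error about 13%.
- Stable person effect 0.4, autoregressive part 0.3 (0.8 per step), noise 0.3: R = [1 − (0.4 + 0.3×0.410)]/[1 − (0.4 + 0.3×0.655)] = 0.477/0.403 = 1.18; 1.974/√1.18 = 1.82; error about 7%.
- Random slopes, with variances for intercept 0.6, slope 0.2 and residual 0.2, and time scaled so that week 12 = 1: change variance = 0.2 + 2×0.2 = 0.6. Expected residual = 0.2 + 0.2×0.15625 = 0.231, where 0.15625 is the sample variance of 0, 0.25, 0.5, 0.75, 1. R = 0.6/0.4625 = 1.30; error about 8%.

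Simulation under no true effect (6,000 or 20,000 runs per scenario) agrees:

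| Assumed truth, five visits | Error, baseline-to-Lab Visit #4 contrast |
|---|---|
| Equal correlation | 4.8–5.1% |
| Small random slopes (variance 0.02 or 0.1, residual 0.5) | 4.7–5.5% |
| Moderate random slopes (slope variance 0.1–0.3, residual 0.2–0.3) | 6.4–10.1% |
| Stable effect and/or noise with decay | 6.1–8.1% |
| Pure autoregression, 0.70–0.95 per step | 12.0–16.4% |

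A test on the change score itself stays at 4.8–5.2%.

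**Seven visits (months 6 and 12 placed at weeks 38 and 64), 252 df, t_crit = 1.969.**

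- Decay in calendar time, 0.7 per 12 weeks: the average of 0.7^(d/12) over the 21 pairs is 0.557. R = 0.3/0.443 = 0.68; 1.969/√0.68 = 2.39; error about 1.7% (simulated 2.4%).
- Autoregression of 0.8 per visit step: mean correlation = (6×0.8 + 5×0.64 + 4×0.512 + 3×0.410 + 2×0.328 + 0.262)/21 = 0.581. R = 0.590/0.419 = 1.41; error about 10% (simulated 10.0%).

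Over all seven-visit scenarios the simulated error of this contrast is 1.1–10.0%.

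**Other tests.** The omnibus arm × time test runs at 4.5–8.0% with five visits and 5.0–9.8% with seven. The arm effect averaged over visits stays at 4.4–5.4%.

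**The case against.** There is a fair case against the point.

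- The article says participant is a random effect. It does not say intercept only. Random slopes are not excluded, lme4 can fit them, and the full protocol or analysis plan may specify them.
- The arm × time term is taken from Sample size and is not listed in the model.
- The assurance follows directly on the Kenward-Roger sentence and reads as a cited reason for that method.
- A two-visit analysis, the setting that reproduces 44, is not affected.
- Pure autoregression, with no stable person component and no measurement noise, is an extreme assumption for a questionnaire.

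All of this stands, and it limits the finding. A reader might infer that the plan's type I error claim is false, or that the primary test will run at 12–16%. The documents do not support that: they give no correlations, the rate is 5% under equal correlation, and less extreme structures give 6–8%. A reader might also infer that the plan claims robustness to a wrong covariance. It does not. Nor is the direction of error fixed, since adding late follow-up can make the Lab Visit #4 contrast conservative.

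What remains is that one random term is named, for an outcome analysed over time at up to seven visits. A random intercept is the natural reading, and the assurance carries no limit to the degrees-of-freedom method.

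**Conclusion.** The point holds in a conditional form. Read as a random-intercept model, the stated primary analysis secures its nominal error for a multi-visit arm × time test only if variances and correlations are equal across visits. The type I error sentence does not provide that security.

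At 22 per arm with complete data, the plausible departure for the baseline-to-Lab Visit #4 contrast with five visits is modest (about 6–10%) and reaches 12–16% only under pure autoregression. With seven visits it can go either way, from about 1–2% up to about 10%. The omnibus test is about 5–8% with five visits and 5–10% with seven. These sizes rest on assumed correlations and on a reading of the random effect, so they show sensitivity and do not demonstrate a failure. The change is worth making because it is cheap and removes the dependence.

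**What to change.** Name the arm difference in FACIT-F at Lab Visit #4 as the primary contrast. Fit weeks 3, 6, 9 and Lab Visit #4 with Lab Visit #2 FACIT-F as covariate; arm, visit and arm × visit as fixed effects; an unstructured residual covariance (4 × 5/2 = 10 parameters); and Kenward-Roger degrees of freedom, in an R package that supports this. Prespecify a fallback structure in case of non-convergence, for example heterogeneous autoregressive. Analyse months 6 and 12 in a separate model. Reword the type I error sentence so that it refers to the degrees-of-freedom method only.

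The cost is a package other than lme4, a few more covariance parameters and a small loss of degrees of freedom. No extra participants or data are needed. Lighter alternatives exist: random slopes would deal with differing rates of change but not with serial decay, and a two-visit primary contrast would avoid the problem but leave weeks 3 to 9 out of the primary analysis.

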### Treatment arms

Both exercise interventions will take place in the Thrive Centre, a fitness facility for people affected by cancer (Faculty of Kinesiology, University of Calgary, Alberta, Canada). The exercise intervention will be delivered in a small group setting by exercise specialists, who have completed specific cancer and exercise training (http://thrivehealthservices.com). Participants in both treatment arms will be supervised by the same exercise specialists. The following prescriptions for aerobic and/or resistance exercise will be followed only where achievable, such as where the exercise is not voluntarily terminated prematurely due to intolerable levels of perceived fatigue, dyspnea or muscle weakness. Where an existing adverse effect of treatment (e.g. shoulder dysfunction) or injury (e.g. knee replacement) limits the performance of a movement, the movement will be restricted, modified or substituted to ensure that there is no pain during or after exercise. In addition, the exercise specialist may adjust intensity or duration based on observation and judgement, particularly in the case of reducing the demands to accommodate day-to-day fluctuations in health or wellbeing in a diverse group of cancer survivors. A decision to discontinue an individual’s intervention will be made by the research team if there is concern that the exercise intervention is causing harm. Upon arrival to supervised exercise sessions (i.e. before exercise), participants will be asked to indicate their fatigue levels using a rating-of-fatigue scale, which quantifies the intensity of the subjective feeling state at a given moment [93]. Should the exercise intervention appear to gradually increase the rating of fatigue over 1–2 weeks, the intensity will be reduced as deemed necessary to ensure the overall wellbeing of the participant. The exercise specialist and research team will communicate regularly regarding individual participants. Participant safety is paramount and any adverse events (related to exercise or not) will be monitored and reported according to the standardized guidelines for reportable events from the independent ethics committee (HREBA.CC). The reasons for dropout from the intervention will be recorded where possible, and no further outcome data will be collected in participants who withdraw from the study.

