### Data analysis

#### Neuromuscular data

The potentiated mechanical response from a single electrical stimulus will be analysed for amplitude of the twitch (Q_tw,pot_), maximal rate of force development and maximal relaxation rate. Voluntary activation using femoral nerve electrical stimulation (VA_FNES_) will be calculated using the interpolated twitch technique where the amplitude of the SIT is normalized to the corresponding Q_tw,pot_ using the equation VA_FNES_ (%) = (1-(SIT/Q_tw.pot_)) × 100 [60]. For TMS, an estimated resting twitch (ERT) will be calculated by taking the y-intercept of a linear regression of the SIT-voluntary force relationship. VA_TMS_ will be subsequently quantified using the equation VA_TMS_ (%) = (1-(SIT/ERT)) × 100 [118]. Where regressions are not linear (defined as *r* < 0.9 [119]), those data will be excluded.

For the evoked EMG responses, the peak-to-peak amplitude and area under the curve of the MEP in all muscle groups will be determined from a selection of data encompassing the biphasic wave. The selection will begin at the first deviation from zero after any stimulation artefact, and end on the return to zero after the biphasic wave. The M-waves evoked in the VL and RF will be analysed using the same method. For the assessment of corticospinal excitability, the VL and RF MEPs will be normalised to an M-wave delivered during a contraction and nearby in time_._ The silent period will be measured from stimulus artefact to the continuous resumption of voluntary EMG, determined by an experimenter experienced in the analysis, using visual inspection of the EMG trace [120].

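### Pre/post-only secondary outcomes are tested by a group × time ANOVA, a change-score comparison that is less precise than baseline adjustment and more exposed to arm-dependent missingness

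*Protocol article*

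**What the plan says.** All references are to the protocol article.

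- **Scope** (Intended statistical analysis): the rule is limited to one class of outcomes: "For secondary outcomes that are assessed pre- and post-intervention only (e.g. neuromuscular measures, sleep parameters, blood biomarkers".
- **Method** (same section): for these, "two-way mixed design ANOVA will be used (group [tailored vs. traditional] × time [pre- vs. post-intervention".
- **Missing data** (same section): "In this case, missing data will be dealt with using list-wise deletion".
- **Primary outcome, for contrast** (same section): FACIT-F "data will be analysed with linear mixed models using R", and "the primary analysis will be conducted on an intention-to-treat basis".
- **Withdrawals** (Treatment arms): "no further outcome data will be collected in participants who withdraw from the study".
- **Further loss** (Data analysis, Neuromuscular data): where the regression behind voluntary activation by TMS has r below 0.9, "those data will be excluded".
- **Numbers** (Sample size): 44 evaluable participants, raised to 52 for 15% attrition. This calculation is for FACIT-F; no secondary outcome has its own.

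**The concern.** In a 2 × 2 mixed design the interaction F statistic is the square of the t statistic comparing mean change between arms. A change score subtracts the whole baseline value, as if the regression slope of post on baseline were 1. When the two visits correlate imperfectly the best slope is smaller, and the excess subtraction adds noise. Adjusting for baseline lets the data set the slope.

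Fixing the slope at 1 also matters when data are missing. If those who remain differ in baseline between the arms, regression to the mean gives the arms different expected changes even with no treatment effect.

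At stake are the neuromuscular, sleep, fitness and biomarker results. The Discussion presents them as a first comprehensive look at how exercise may improve fatigue, and the dissemination section foresees separate papers on some of them. With about 44 completers, precision is scarce.

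**Working it through.** **1. The plan's own figures.** No figure is given for the secondary outcomes. The primary figure reproduces if the stated 0.44 is entered as f = 0.44/2 = 0.22 with an assumed ρ = 0.5. The noncentrality is N·f²·m/(1−ρ) = 44 × 0.0484 × 2/0.5 = 8.52 on 1 and 42 degrees of freedom, which gives power 0.814. Then 44/0.85 = 51.8, rounded up to 52. So 44 is the number of completers the trial already expects.

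**2. Precision.** Take equal variance σ² at both visits and correlation ρ. Per participant, in units of σ²:

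- change score (the planned interaction test): 2(1−ρ)
- post value adjusted for baseline: 1−ρ²
- ratio: (1−ρ²)/[2(1−ρ)] = (1+ρ)/2

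| ρ (assumed) | Change score | Adjusted | Ratio | 44 completers are worth |
|---|---|---|---|---|
| 0.3 | 1.40 | 0.91 | 0.65 | 44/0.65 = 67.7 |
| 0.5 | 1.00 | 0.75 | 0.75 | 44/0.75 = 58.7 |
| 0.7 | 0.60 | 0.51 | 0.85 | 44/0.85 = 51.8 |
| 0.8 | 0.40 | 0.36 | 0.90 | 44/0.90 = 48.9 |
| 0.9 | 0.20 | 0.19 | 0.95 | 44/0.95 = 46.3 |

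The last column is the number of participants the planned test would need for the same precision. At ρ = 0.5 the change score is no more precise than the post value alone (variance 1.00), and below 0.5 it is worse. The price of adjustment is one error degree of freedom, 42 to 41.

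**3. Small-sample check.** Simulation with 26 per arm, 15% of post values missing completely at random, and 6,000 runs per setting. Standard errors in SD units:

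| ρ | Change score | Adjusted | Variance ratio |
|---|---|---|---|
| 0.5 | 0.297 | 0.262 | (0.262/0.297)² = 0.78 |
| 0.7 | 0.237 | 0.220 | (0.220/0.237)² = 0.86 |
| 0.8 | 0.190 | 0.181 | (0.181/0.190)² = 0.91 |

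The gain is close to the formula, slightly reduced by the small sample. Both methods used the same completers.

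**4. Does keeping baseline-only participants help?** At ρ = 0.5, a mixed model with arm-specific means that keeps every baseline value has a standard error of 0.292, against 0.297 for complete-case change scores. Almost nothing is recovered.

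**5. Bias.** Given baseline x, the expected change is (ρ−1)x plus the arm effect. If completers' mean baseline differs between arms by Δ, the change-score contrast is biased by (ρ−1)Δ. In the simulation with no true effect:

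| Missingness | ρ = 0.5 | ρ = 0.7 | ρ = 0.8 |
|---|---|---|---|
| Same dependence on baseline in both arms: change score | −0.002 | 0.001 | 0.000 |
| Opposite dependence in the two arms: change score | −0.129 | −0.077 | −0.054 |
| Opposite dependence in the two arms: adjusted | 0.002 | 0.002 | −0.002 |

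The middle row fits the formula with Δ of about 0.26 SD: 0.129/0.5 = 0.26, 0.077/0.3 = 0.26, 0.054/0.2 = 0.27.

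**The case against.** The mixed ANOVA is a common and legitimate test, and it does use the baseline through the change score. For highly correlated measures little is left to gain: 5% to 10% of variance at ρ of 0.8 to 0.9. The outcomes are secondary and unpowered. The plan already promises 95% intervals for mean differences and open code. All of this stands and limits the weight of the point.

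A reader might infer more than the documents support:

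- **That the ANOVA throws participants away and adjustment would bring them back.** An adjusted model also needs a post value, and nothing is collected after withdrawal. The fall from 52 to 44 is attrition that the sample size already allows for.
- **That list-wise deletion is valid only if data are missing completely at random, or biased whenever weaker participants drop out.** When dropout depends on baseline in the same way in both arms, no bias appeared. Bias needs dependence that differs by arm. This is conceivable, because only one arm's exercise is matched to baseline deficits and participants are unblinded, but the protocol does not predict it.
- **That every secondary result is affected.** The rule covers pre/post-only outcomes. Table 2 gives further time points for the ESAS-r, CES-D, BPI-sf and GLTEQ.
- **That all voluntary-activation data are at risk.** The r < 0.9 exclusion concerns the TMS measure; the femoral-nerve measure uses no regression.
- **That the gain can be stated as a required sample size.** In the sample size section, "A standardized mean difference of 0.44 was used" refers to FACIT-F. No secondary outcome has a target effect.

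**Conclusion.** The point holds as a matter of efficiency, with a conditional protection against bias. For pre/post-only secondary outcomes the planned interaction test has a larger variance than baseline adjustment at any ρ below 1, apart from the small cost of estimating one slope. Adjustment cuts the variance by about 25% at ρ = 0.5, 15% at 0.7 and 10% at 0.8. These figures assume randomized arms, equal variances at the two visits and a linear relation to baseline; ρ is assumed, and will differ between outcomes.

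The bias in the planned test was 0.05 to 0.13 SD in an illustrative case with 15% missing and baseline dependence running in opposite directions in the two arms. It is zero when the dependence is the same in both. Adjustment removes it when missingness within arm depends on baseline alone.

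The primary analysis and the stated sample size are not affected. The change is worth making because it is almost free, not because the planned test is invalid.

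**What to change.** For secondary outcomes measured only pre- and post-intervention, replace the ANOVA interaction test with a linear model of the post value on arm and the baseline value of the same measure. Report the adjusted arm difference with its 95% confidence interval and the number analysed, and state the missing-data assumption.

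As an alternative, fit a mixed model to both visits with a common baseline mean for the two arms. It also keeps participants who have a post value but no usable baseline. There should be few, since randomization follows completion of the baseline assessments; voluntary activation by TMS, with its linearity exclusion, is the likeliest case.

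The cost is wording, a few lines of R code and one error degree of freedom. R and lme4 are already planned for the primary outcome. Adding all the minimization factors should not be bundled in as if equally cheap: sex (1), age group (3) and cancer type (4) add 1 + 3 + 4 = 8 parameters with about 44 completers, and the gains shown here do not allow for that.

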### Dissemination and data sharing policy

The results for primary and secondary outcomes will be disseminated regardless of the magnitude or direction of the effect. The primary research aim will be addressed in a main publication reporting the results of the primary analysis i.e. the effect of treatment arm on CRF severity. Due to the number of secondary outcomes, additional publications may be warranted to provide in-depth analysis of, for example, data related to neuromuscular fatigue, sleep or ROF. Scientific and administrative information about the results of the trial will be submitted to the ClinicalTrials.gov results database. Participants will be informed about their personal results in a participant report written in plain language, within 4 weeks of Visit #4. No later than 2 years after the final follow-up assessment, an anonymized, de-identified dataset will be made openly available to an appropriate data archive for sharing purposes.

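### For pre/post secondary outcomes, no signed between-arm difference in change with an interval is planned unless the interaction is significant, and possibly not even then

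*Protocol article*

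**What the plan says.** All of this is in the Intended statistical analysis section of the protocol article, unless noted.

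- Model for outcomes measured before and after only (neuromuscular measures, sleep parameters and blood biomarkers are the examples given): "two-way mixed design ANOVA will be used (group [tailored vs. traditional] × time [pre- vs. post-intervention" (the closing brackets follow).
- Missing data for these outcomes: "In this case, missing data will be dealt with using list-wise deletion".
- Follow-up tests: "Following a significant interaction, pairwise comparisons will be conducted with a Bonferroni adjustment". The significance threshold is p < 0.05.
- Effect size for the ANOVA terms: "For main and interaction effects, partial eta squared will be computed as an effect size estimate". No significance condition is attached.
- Effect size for the follow-up tests: Cohen's d, assigned to the pairwise comparisons.
- Intervals: the next sentence is "This will be supplemented with 95% confidence intervals for mean differences".
- Dissemination and data sharing policy: "The results for primary and secondary outcomes will be disseminated regardless of the magnitude or direction of the effect".

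No sentence names the between-arm difference in change as a quantity to be estimated, and the section does not list which pairwise comparisons will be run.

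**The concern.** With two arms and two time points, the interaction is a single one-degree-of-freedom contrast: the difference between arms in pre-to-post change. It is the treatment effect itself. It needs no follow-up test, only an estimate and an interval.

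The plan attaches the interpretable quantities to a later step that runs only if the interaction is significant. Three consequences follow.

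1. A non-significant outcome is left with partial eta squared, which cannot show which arm did better, by how much in the outcome's own units, or how precisely.
2. A significant outcome goes on to pairwise comparisons. The usual ones (pre against post within an arm, or arm against arm at one time) are not the difference in change, so the treatment effect may still go unreported.
3. Differences reported only after passing a significance test are, on average, too large when the true effect is small or moderate for the sample size.

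The secondary outcomes carry much of the trial's stated contribution, the examination of pathways by which exercise may reduce fatigue. A reader of those results needs to tell no effect from an imprecise estimate.

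**Working it through.** **Inputs.** From the Sample size section: standardised mean difference 0.44, α 0.05, power 0.80, total 44, attrition 15%, enrolled total 52. Allocation is 1:1 (Methods/design). The pre-post correlation is not stated, so I assume 0.5 and also show 0.7. List-wise deletion at the planned attrition leaves about 44 participants, or 22 per arm. Effects are in units of the outcome's SD, assumed equal at both times.

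**The plan's own figure.** For a within-between interaction, λ = f² × N × m / (1 − ρ). Taking f = 0.44/2 = 0.22, m = 2 and ρ = 0.5:

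- N = 44: λ = 0.0484 × 44 × 2 / 0.5 = 8.52, power 0.814.
- N = 42: power 0.795.

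So 44 is the smallest even total reaching 0.80, and 44/0.85 = 51.8, rounded up to 52. Both figures reproduce. In terms of the difference in change, √8.52 = 2.92 standard errors of 0.3015 SD is 0.88 SD, so 0.88 SD is included below.

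**What must be observed to pass.** The SD of change is √(2(1 − ρ)), which is 1 at ρ = 0.5. The critical difference in change is t(0.975, 42) × √(2/22) = 2.018 × 0.3015 = 0.61 SD. With 26 per arm it is 0.56 SD.

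**What is reported after passing.** Simulation, 400,000 draws per row, 22 per arm:

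| Pre-post correlation | True difference in change | Pass p < 0.05 | Mean size among those passing | Ratio to truth |
|---|---|---|---|---|
| 0.5 | 0.20 SD | 10% | 0.72 SD | 3.6 |
| 0.5 | 0.44 SD | 30% | 0.78 SD | 1.8 |
| 0.5 | 0.88 SD | 82% | 0.98 SD | 1.11 |
| 0.7 | 0.20 SD | 13% | 0.57 SD | 2.85 |
| 0.7 | 0.44 SD | 45% | 0.64 SD | 1.45 |
| 0.7 | 0.88 SD | 96% | 0.90 SD | 1.02 |

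At 26 per arm, correlation 0.5 and a true 0.44 SD, 34% pass and average 0.73 SD (1.66-fold). Without selection, the 95% interval covers the truth about 95% of the time in every row. Among outcomes that pass, at 22 per arm and correlation 0.5, coverage is 70% at 0.20 SD and 91% at 0.44 SD.

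**The arm difference at post.** The table describes the difference in change. If the reported contrast is instead arm against arm after the intervention, and there is no true baseline difference, its regression on the difference in change has slope (1 − ρ) / (2(1 − ρ)) = 0.5. At correlation 0.5 and a true 0.44 SD, its mean after selection is 0.44 + 0.5 × (0.78 − 0.44) = 0.61 SD, or 1.4-fold.

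**What partial eta squared hides.** At 22 per arm and correlation 0.5, an observed difference in change of +0.4 SD gives t = 0.4/0.3015 = 1.33 and partial eta squared = 1.76/(1.76 + 42) = 0.04. An observed −0.4 SD gives the same 0.04. The interval for the first is 0.4 ± 0.61, or −0.21 to 1.01 SD.

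**The case against.** The strongest reply has five parts.

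- **An effect size is planned for every outcome.** This stands. A reader might infer that non-significant outcomes get no estimate of effect at all. That goes too far: partial eta squared is computed regardless, and with the error degrees of freedom it returns F and |t|. If cell means are published, the sign can be recovered. What is missing is a planned estimate with sign, unit and interval.
- **The interval sentence is ambiguous.** This stands in part. It follows the sentence on pairwise comparisons and most naturally belongs to it, but it could refer to effect-size reporting as a whole. No text expressly limits intervals to significant outcomes. Even on the generous reading, the mean difference meant is not identified as the difference in change.
- **Dissemination is promised whatever the size or direction.** This stands, with registry results, open data and open code alongside. It rules out inferring that non-significant outcomes would go unpublished. It does not say in what form they will appear, and an unsigned statistic cannot convey direction.
- **The pairwise contrasts are not listed.** This stands. One might infer that the arms will be tested against each other at baseline, or that significance in one arm only will be read as a treatment effect. The article says neither.
- **Tabulation of secondary results belongs in a full analysis plan, and ANOVA with conditional follow-up is conventional.** This does not remove the point. The article states a rule that makes the comparisons conditional; it is not merely silent on detail. It is fair that only secondary outcomes are affected, since the primary outcome has its own mixed model.

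**Conclusion.** The point holds as a defect in a stated reporting rule for the pre/post secondary outcomes. Pairwise comparisons and Cohen's d, and on the natural reading the intervals, depend on a significant interaction. The treatment effect itself is summarised only by an unsigned, unit-free statistic with no stated interval.

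The size of the selection effect is conditional. At 22 per arm, correlation 0.5 and a true difference in change of 0.44 SD, about 30% of outcomes pass. Among them the difference in change is overstated about 1.8-fold and the arm difference at post about 1.4-fold; at correlation 0.7 the former is about 1.45-fold. At a true 0.88 SD the problem nearly disappears (82% pass, about 11% overstatement).

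Two broader statements are tempting and not supported. That most outcomes will lack an interpretable estimate depends on true effects and correlations the documents do not give. That published differences will be inflated 1.8-fold applies only if the reported quantity is the difference in change, which the planned pairwise comparisons need not include.

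**What to change.** State that, for every secondary outcome and whatever the interaction p-value, the between-arm difference in change (or the baseline-adjusted post-intervention difference) will be reported in original units with a 95% confidence interval. Do not make this estimate conditional on a significant interaction. Partial eta squared and any pairwise contrasts may stay as supplements.

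The cost is a few sentences in the analysis section and slightly longer results tables. No new data are needed. The difference in change is the interaction contrast of the ANOVA already planned, and a baseline-adjusted difference comes from a comparable model on the same data.
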